#### HIV Risk Behavior

The Behavioral Risk Assessment [56] measured HIV risk behavior. This instrument recorded data on participants' sociodemographic characteristics (gender identity, sexual identity, age, race/ethnicity, HIV status, educational attainment, housing status), substance use in the previous 30 days (injection and noninjection drug use and safe needle use protocol), number and gender of sexual partners in the previous 30 days (main, casual, anonymous, exchange and male, female, male-to-female preoperative transgender, female-to-male preoperative transgender), and details about the participants' three most recent sexual encounters within the previous 12 months (partner type, number of partners in the encounter, HIV status of partner[s], sexual activities during the encounter, substance use by participant and partner[s], location of sexual encounter).

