## Methods

### Study Design

The study began with formative research to develop the intervention. This was followed by a 2-group randomized controlled trial (RCT) in which individuals receiving usual care for HIV were randomly assigned to receive either TXT-CBT or an informational pamphlet concerning HIV and substance use. The trial was conducted and reported in accordance with the Consolidated Standards of Reporting Trials (CONSORT) guidelines [43]. Face-to-face assessments were conducted at baseline and weeks 4, 8, 12, and 24. Phone-based assessments of ART adherence were also conducted at each of these timepoints.

All study procedures were approved by the University of California, Los Angeles Institutional Review Board. This trial is registered at ClinicalTrials.gov [NCT01884233].

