### Intervention Content

The intervention comprised one CBT-based face-to-face counseling session with a master’s level clinician followed by 12 weeks of daily text messages. The messages included medication reminders plus 2 or 3 additional messages on the topic of addiction recovery and associated risk behaviors. Participants selected the desired frequency and time at which to receive their medication reminder messages. Participants enrolled thus far typically require 1 or 2 medication reminders daily. As such, participants receive 4 or 5 text messages daily. Of the 14 to 21 messages per week that are not medication reminders, approximately half of the message content pertains to CBT skills for drug relapse prevention with the remaining half split evenly between content concerning common HIV risk behaviors and ways to reduce them and the importance of ART adherence coupled with behavioral strategies to promote adherence.

During the clinician-delivered CBT session, a number of variables upon which the intervention was tailored or individualized were identified, including the top 3 barriers to ART adherence for the individual, with corresponding coping skills training; the participant’s first name; specific times of day at which medication reminders are needed; and motives for quitting substance use.

Content had both informational and interactive components to model the balance between psychoeducation and counseling in traditional clinician-delivered CBT. The remaining texts provided psychoeducation, tips, suggestions, and reminders to facilitate the use of cognitive and behavioral strategies to prevent substance relapse, improve ART adherence, and reduce HIV risk behaviors. Relapse prevention messages comprised 50% of those sent to participants each week (see Textbox 1). The 12-week intervention is staged such that each week a new specific coping skill was introduced:

1. Behavioral techniques such as scheduling and engaging in alternative rewarding activities to prevent boredom and maintain a sober lifestyle

2. Opioid withdrawal symptoms, similarities between stress and withdrawal symptoms, and coping techniques to prevent relapse in the face of these symptoms

3. Stress as a relapse precipitant, with descriptions of stress management techniques in the form of easy-to-implement tips

4. Common triggers to opioid relapse with suggestions on how to eliminate or minimize triggers

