#### Treatment As Usual

All participants were receiving usual care for HIV, which comprised pharmacological management by a physician in an infectious disease clinic setting. Generally, participants were scheduled for monthly visits with their physician and quarterly assessment of viral load and CD4 counts.

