#### ART Adherence

ART adherence was assessed using both phone-based UPCs and viral load data. Both home- and phone-based UPCs have been shown to be reliable and valid measures of HIV treatment adherence, yielding comparable data to electronic medication monitoring [57,58] and significant correspondence with plasma viral load [59]. At the initial research visit, participants were trained by an intake assessor and a phone-based pill counter on the telephone in procedures for conducting UPCs. Training focuses on instructing participants to organize and count their pills. The first UPC was conducted within 1 week of the training, with subsequent monthly UPCs at unannounced times during and after the intervention through follow-up at week 24. All UPCs were conducted for each ART medication the participant is taking. Pharmacy information from pill bottles was also collected to verify the number of pills dispensed between calls. A medication adherence score was then calculated as the ratio of pills counted to pills prescribed, taking into account the number of pills dispensed. Using this method, the adherence score represents the percentage of pills taken as prescribed averaged across medications [60].

Viral load served as a biological indicator of adherence. Consistent with the typical frequency with which viral load is assessed in clinical settings, data concerning viral load was collected at baseline, treatment end, and follow-up. Participants either provided us with a copy of their latest viral load results or signed a medical release of information allowing us to obtain their viral load results directly from their medical provider.

**Table 1 table1:** Key variables and measurements.

	Variables	Measurements	Screen	BL	Week 4	Week 8	Week 12	Follow-up

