**Secondary outcomes**								
	Medication compliance	Self-report^c^		x	x	x	x	x
	Behavioral strategies	Self-report^c^		x				x
	Depression	PHQ-9^c,d^		x	x	x	x	x
	Anxiety	OASIS^c,e^		x	x	x	x	x
	Drug-taking self-efficacy	Drug-Taking Confidence Questionnaire^c^		x			x	x
	Health-related quality of life	SF-12^c,f^		x			x	x
	Readiness for change	SOCRATES-D^c,g^		x				

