#### Behavioral Strategies for Adherence

From a 25-item behavioral strategies checklist developed by Kalichman et al [60], participants were asked to indicate how often they have used these strategies during the past 3 months. Answer choices are never, sometimes, often, very often, and always. Examples of strategies included in the questionnaire are “used a pill box organized by day of the week” and “used bedtime as a reminder to take medications.”

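### Two recall windows fit the 12 treatment weeks poorly: one part of the HIV risk outcome can carry over pre-randomisation encounters, and the strategies checklist misses nearly all of treatment

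*Protocol article*

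**What the plan says.** All locations are in the Protocol article.

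- **Timing.** Intervention Content describes one counselling session "followed by 12 weeks of daily text messages". Study Design states: "Face-to-face assessments were conducted at baseline and weeks 4, 8, 12, and 24".
- **HIV risk behaviour (primary).** The HIV Risk Behavior section gives the instrument two kinds of window. Drug use, needle use and partner counts refer to the past month, for example "number and gender of sexual partners in the previous 30 days". Encounter detail (partner type, partner HIV status, activities, substance use, location) is taken for the "three most recent sexual encounters within the previous 12 months". Table 1 schedules the instrument at baseline, week 12 and follow-up.
- **Strategies checklist (secondary).** Behavioral Strategies for Adherence asks participants "how often they have used these strategies during the past 3 months". The Table 1 row "Behavioral strategies" is marked at baseline and follow-up only; the week-12 cell is empty.
- **Viral load (listed with pill counts under ART adherence, a primary outcome).** It is collected at baseline, treatment end and follow-up from clinic records: "Participants either provided us with a copy of their latest viral load results", or the participant signed a release. Treatment As Usual says that clinics generally provide "quarterly assessment of viral load and CD4 counts".

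**The concern.** A post-baseline measure should describe the period in which the intervention could have acted. The encounter items look back much further than the time since randomisation, so some of what is recorded at week 12 may be behaviour already reported at baseline. Such carry-over occurs in both arms and would mainly draw them together, diluting any difference on those items.

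The checklist has the opposite problem. Its baseline window ends when treatment starts, and its week-24 window opens only as treatment is ending. It therefore says almost nothing about whether participants used the taught strategies while the messages were being sent.

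The viral load point is of the same kind but smaller: a clinic result on file at week 12 may be weeks old.

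The trial is a pilot with 25 participants planned per group, and one purpose is to explore effect sizes before a larger trial. An effect estimate diluted by old data, or taken from the wrong period, would misinform that planning.

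**Working it through.** The plan states no figure of its own on this point, so there is none to reproduce. The check is calendar arithmetic.

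**Inputs.** Randomisation and treatment start are taken as day 0 (an assumption), treatment as days 0 to 84, and follow-up as day 168. The windows from the article are 12 months (365 days) for encounter detail, 30 days for the other risk items, and 3 months (90 to 92 days) for the checklist. Quarterly testing is taken as every 84 to 91 days.

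**1. Encounter detail.** Pre-randomisation days in the window = window − visit day.
- Week 12: 365 − 84 = 281 days (77%).
- Week 24: 365 − 168 = 197 days (54%).
- For the 30-day items the result is 0 at both visits, because the windows open on days 54 and 138.

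Twelve months is an outer limit, since only the last three encounters count. Earlier encounters enter only if fewer than three have occurred since randomisation. The article gives no encounter rate, so a range is assumed, with Poisson counts and a month of 30.4 days:

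P(fewer than 3) = e^(−m)(1 + m + m²/2), where m = rate × days / 30.4.

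| Assumed rate per month | Week 12: m | P | Week 24: m | P |
|---|---|---|---|---|
| 0.5 | 1.38 | 84% | 2.76 | 48% |
| 1 | 2.76 | 48% | 5.53 | 9% |
| 2 | 5.53 | 9% | 11.05 | 0.1% |

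**2. Strategies checklist.** Treatment days covered at week 24 = 84 − (168 − window).
- 90 days: 84 − 78 = 6.
- 92 days: 84 − 76 = 8.
- Not covered by any administration: 76 to 78 of 84 days (90 to 93%).
- If the checklist were also given at week 12, a 91-day window would open on day −7 and cover all 84 treatment days.

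**3. Viral load at week 12.** With regular testing every I days at a random phase, mean age = I/2 and P(drawn before randomisation) = max(0, 1 − 84/I).
- I = 84: mean 42 days (6 weeks), P = 0.
- I = 91: mean 45.5 days (6.5 weeks), P = 7/91 = 8%.
- I = 120, as an illustration of late tests: P = 30%.
- At week 24 the 84 becomes 168, so P = 0 unless the interval exceeds 168 days.

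**4. Comparison with Timeline Followback.** Its 30-day windows at weeks 4, 8 and 12 open on days −2, 26 and 54, so together they cover the whole of treatment. Its 90-day window at follow-up opens on day 78.

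**The case against.** The strongest reply concerns reach. The article lists what the risk instrument records, not which items are scored, and its examples of dependent variables include no encounter item. The 30-day items may already be the intended outcome. That stands: the point concerns one component of the HIV risk outcome and disappears if that component is not analysed.

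A reader might infer that two primary outcomes are compromised, or that the plan's look-back windows are misaligned in general. The article does not support either reading. The 30-day risk items hold no pre-randomisation days after baseline, ART adherence is also measured by monthly unannounced pill counts, and the Timeline Followback windows fit the treatment period closely.

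A reader might also take the 77% as the share of contaminated data. It is only the share of the permitted window. Actual carry-over depends on encounter rates that the article does not give, and is 9% at two per month.

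For viral load, one could note that 33% (28/84) to 38% (35/91) of week-12 values would have been drawn before week 4. Most of those draws follow randomisation: at a 91-day interval, 28 of the 35 days fall in treatment weeks 0 to 4 and only 7 before. Using clinic results is a deliberate choice, and a draw-date rule may sit in the full protocol.

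Finally, asking about strategies at week 24 is a legitimate way to measure retained use. It does not measure use during treatment.

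**Conclusion.** The point holds as an inexpensive improvement of limited scope.

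- **Encounter detail.** The stated window and visits allow the same pre-randomisation encounters to appear at baseline and at week 12, and less often at week 24. The window arithmetic is firm. The proportion of participants affected (9 to 84% at week 12, 0.1 to 48% at week 24) rests entirely on assumed rates and the Poisson model. Dilution is the likely consequence, but its size cannot be derived from the article.
- **Checklist.** This is firm, because window and visits are both stated: 6 to 8 of 84 treatment days are covered. It is a secondary outcome.
- **Viral load.** This is the lesser point. The week-12 value averages about 6 weeks old and is pre-randomisation in about 0 to 8% of cases if quarterly testing is kept, more if tests are missed. The problem hardly arises at week 24.

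**What to change.** 1. **HIV risk.** State that the post-baseline outcome is based on the 30-day items. Alternatively, at weeks 12 and 24 ask only about encounters since the instrument was last given (baseline and week 12 respectively). The first option needs no new data but gives up the encounter-level detail as an outcome. The second changes the question for visits still to come. Filtering stored answers by date should not be relied on, because the article lists no encounter date among the recorded items.
2. **Checklist.** Add it to the existing week-12 web battery for participants not yet past that visit. The cost is 25 more web items at a visit that already takes place. Data collection was under way when the article was written, so week-12 data will be incomplete. For participants already past it, interpret the week-24 answers as post-treatment use only.
3. **Viral load.** Record the draw date of every result and do not count one drawn before randomisation as a treatment-end value. This loses about 0 to 8% of week-12 values under quarterly testing and more if tests are missed. Any draw-date window should not lie mostly after treatment end or run past the last assessment, since that would replace one misalignment with another.

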#### ART Adherence

ART adherence was assessed using both phone-based UPCs and viral load data. Both home- and phone-based UPCs have been shown to be reliable and valid measures of HIV treatment adherence, yielding comparable data to electronic medication monitoring [57,58] and significant correspondence with plasma viral load [59]. At the initial research visit, participants were trained by an intake assessor and a phone-based pill counter on the telephone in procedures for conducting UPCs. Training focuses on instructing participants to organize and count their pills. The first UPC was conducted within 1 week of the training, with subsequent monthly UPCs at unannounced times during and after the intervention through follow-up at week 24. All UPCs were conducted for each ART medication the participant is taking. Pharmacy information from pill bottles was also collected to verify the number of pills dispensed between calls. A medication adherence score was then calculated as the ratio of pills counted to pills prescribed, taking into account the number of pills dispensed. Using this method, the adherence score represents the percentage of pills taken as prescribed averaged across medications [60].

Viral load served as a biological indicator of adherence. Consistent with the typical frequency with which viral load is assessed in clinical settings, data concerning viral load was collected at baseline, treatment end, and follow-up. Participants either provided us with a copy of their latest viral load results or signed a medical release of information allowing us to obtain their viral load results directly from their medical provider.

**Table 1 table1:** Key variables and measurements.

	Variables	Measurements	Screen	BL	Week 4	Week 8	Week 12	Follow-up

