### Outcome Measures

See Table 1 for an overview of the outcome measures. Primary outcomes included ART adherence, substance use, and HIV risk behaviors. ART adherence was assessed by phone using an unannounced pill count (UPC) procedure. All other outcome measures were administered in face-to-face interviews, with some clinician-administered measures and the majority of the assessments conducted using a Web-based data entry system. Participants were compensated in gift cards as follows: $40 for the baseline assessment, $20 for each monthly face-to-face assessment, and $20 for each phone-based pill count procedure. Additionally, for bringing in photocopies of viral load and CD4 count assay reports from their primary HIV care provider, participants were compensated $20 at baseline (BL), treatment end, and follow-up.

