### Statistical Analyses

Analyses in the pilot study will allow basic description of the sample in terms of distributional characteristics, variability, and missing data as well as examination of possible effect sizes in comparing the groups. Preliminary analyses will include descriptive statistics and confidence intervals, computation of scale scores, and assessment of reliability. Exploratory analyses will use a random effects regression approach to examine group differences across the repeated observations (baseline, treatment end, and follow-up) as specified in each of the study aims. This type of model accommodates the (potentially correlated) repeated measures and allows for inclusion of covariates (ie, subject characteristics on which the groups differ at admission) and additional repeated observations for some measures (eg, viral load at baseline, treatment end, and follow-up). The pilot sample size of 25 per group should allow detection of an effect size of approximately d=.7 in differential change in outcomes from baseline to follow-up, assuming a moderate correlation of 0.50 over time and allowing attrition of up to 20% (power=.80, one-tailed alpha=.05). This detectable effect size would translate to a differential change of about 19 points on the ART adherence composite score assuming an average (across time) pooled (across groups) standard deviation of about 27, as found by Safren [11] for a specialized CBT intervention for HIV-infected individuals. Safren et al found a differential change of approximately 25 points.

Separate analyses will address each measure in aims 1, 2, and 3. For example, analyses for aim 2 will include as dependent variables urine toxicology results for opioids and stimulants, ART adherence scores, health-related quality of life scores from the SF-12, and select items from the ASI indicating number of days in the past month utilizing health services. Analyses for aim 3 will include correlations between changes in self-efficacy (Drug-Taking Confidence Questionniare) and treatment retention and substance use during and after treatment.

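### Week-12 and week-24 viral load depends on continued study participation for anyone who supplies copies and has signed no release; a release sought from everyone at baseline would remove this for those still in HIV care

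*Protocol article*

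**What the plan says.** The ART Adherence section gives viral load a definite role: "Viral load served as a biological indicator of adherence". Table 1 lists it, with CD4 count, under primary outcomes at baseline, week 12 and follow-up (week 24). The same section confirms the schedule: "data concerning viral load was collected at baseline, treatment end, and follow-up".

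The collection rule offers two routes: "Participants either provided us with a copy of their latest viral load results or signed a medical release of information", the second "allowing us to obtain their viral load results directly from their medical provider". The copy route carries an incentive. Under Outcome Measures, "for bringing in photocopies of viral load and CD4 count assay reports from their primary HIV care provider, participants were compensated $20" at each of the three time points. No payment for signing a release is mentioned.

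The test itself belongs to usual care. The Treatment As Usual section describes "quarterly assessment of viral load and CD4 counts" as the general pattern, and no study blood draw is described. The article does not say that everyone signed a release, when releases were signed, or how many participants used each route.

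**The concern.** A clinic result can exist whether or not the person attends research visits. Every participant was in HIV care and on a recent ART prescription at entry, so there was a provider to ask in every case. Under the two-route rule, however, a participant who has signed no release must bring the report. If that person stops attending, the week-12 or week-24 value is missing from the trial although the clinic has it.

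Three things make this worth attention.

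- **Relation to outcome.** People who leave a trial of drug use and ART adherence may well be those whose adherence is worse, so the missing values may not resemble the observed ones.
- **Relation to arm.** The Randomization section states that neither staff nor participants were blinded. The weekly calls are confined to the TXT-CBT arm (Table 1, first footnote), and the Limitations section concedes that imbalance. Retention, and with it the supply of copies, could differ between arms.
- **Lost opportunity.** The other primary adherence measure, the phone pill count, also needs the participant's cooperation. Provider-supplied viral load is the one adherence measure in Table 1 that need not depend on it.

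**Working it through.** **The plan's own figure.** The attrition allowance appears only in the power statement in Statistical Analyses, which gives a detectable d of about 0.7 with 25 per group, correlation 0.50, power 0.80, one-tailed alpha 0.05 and "allowing attrition of up to 20" per cent. With 20 per group left and baseline adjustment:

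d = (1.645 + 0.842) × √(2/20) × √(1 − 0.50²) = 0.786 × 0.866 = 0.68.

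This agrees with about 0.7, and 0.7 × 27 = 18.9 agrees with the stated 19 points. That figure concerns the adherence score. It says nothing about how viral load is retrieved, so only the attrition ceiling carries over.

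**Inputs for viral load**

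- N = 50 (Sample Size) and attrition of at most 20% (Statistical Analyses), so at most 0.20 × 50 = 10 dropouts.
- s = share of dropouts who had signed a release. Not given; taken from 0 to 1.
- c = share of dropouts whose clinic still measures viral load. Not given; taken from 0 to 1.

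**Formula.** Count every retained participant as having a value, and treat signing and remaining in care as unrelated among dropouts:

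share with a later viral load = 0.80 + 0.20 × s × c.

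| Participants of 50 with a value | c = 0 | c = 0.5 | c = 1 |
|---|---|---|---|
| s = 0 (no dropout signed) | 40 | 40 | 40 |
| s = 0.5 | 40 | 42.5 | 45 |
| s = 1 (all signed) | 40 | 45 | 50 |

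**Avoidable loss.** The gain from moving to s = 1 is 10 × c × (1 − s):

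- s = 0, c = 1: 10 × 1 × 1 = 10 participants.
- s = 0.5, c = 1: 10 × 1 × 0.5 = 5.
- s = 0.5, c = 0.5: 10 × 0.5 × 0.5 = 2.5.
- c = 0, any s: 0.
- s = 1, any c: 0.

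The avoidable loss is therefore between 0 and 10 of 50. The upper end needs attrition at the ceiling, no dropout with a release, and every dropout still tested. Refusals or withdrawn releases would lower the gain.

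**The case against.** The strongest reply is that the plan already has a release route, so dropouts who signed can be followed through their provider. How many signed, and when, is the sort of detail an article leaves to the full protocol or consent form. The trial is a pilot sized for feasibility with exploratory analyses, and the adherence outcome does not rest on viral load alone. Pill counts are unannounced, made by phone at every time point and checked against pharmacy information. The remedy also keeps a copy route for those who decline, so it changes the default and the timing more than the principle.

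Most of this stands, and it limits the size and weight of the point. It does not remove it. The two-route rule is stated, and so is the payment attached to one route. For a participant without a release the gap follows directly.

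A reader might infer more than the documents support:

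- **That viral load is lost for everyone who drops out.** The release route contradicts this.
- **That a universal release would also keep it for people who fall out of care.** Testing is part of usual care, so for them there is no result to retrieve.
- **That suppression is overstated by a known amount.** If 70% of an arm and 20% of its dropouts were suppressed, completers would show (0.70 − 0.20 × 0.20)/0.80 = 82.5%, an excess of 12.5 points. The article gives neither rate and defines no suppression endpoint. The sum also needs every dropout to lack a release.
- **That participants may pick which report to bring.** The stated rule asks for the latest result.

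**Conclusion.** The point holds in a limited form. For participants on the copy route with no signed release, a listed primary measure at weeks 12 and 24 depends on their staying in the study, although usual care may still produce the value. The payment favours that route. The number affected is unknown and lies between 0 and 10 of 50 under the attrition the article allows.

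Whether the loss is related to adherence or differs by arm is plausible, given the lack of blinding and the unequal contact, but no figure in the article shows it. No size of bias can be stated. This is a cheap improvement to a collection rule; it does not show that the planned comparison is invalid.

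**What to change.** Replace the two-route rule with a default:

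1. Ask every participant at the baseline visit to sign the existing release, valid through week 24 plus a stated laboratory window.
2. Use provider-supplied results as the source for viral load and CD4 at all three time points.
3. Keep the participant's copy as a backup for those who decline the release.
4. Retrieve results after a participant leaves the study, unless the release is withdrawn.

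The Results section describes data collection as ongoing, so releases could still be sought from active participants. The larger trial foreseen under Limitations could adopt the rule from the start.

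The cost is one existing form moved to baseline, records requests for up to 50 people, and some refusals. Two gaps remain. People who fall out of HIV care still have no value, and a clinic result need not fall near week 12 or 24, so the date of each result should be recorded with it.
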